## Abstract

**Background:**

Despite the high prevalence of comorbid chronic pain and depression, this comorbidity remains understudied. Meditation has demonstrated efficacy for both chronic pain and depression independently, yet there have been few studies examining its effectiveness when both conditions are present concurrently. Furthermore, while meditation is generally accepted as a safe and effective health intervention, little is known about how to implement meditation programs within or alongside the health care system.

**Methods:**

We will conduct a hybrid type 1 effectiveness–implementation evaluation. To measure effectiveness, we will conduct a randomized controlled trial comparing Sahaj Samadhi Meditation and the Health Enhancement Program in 160 people living with chronic pain, clinically significant depressive symptoms, and on long-term opioid therapy. Changes in depressive symptoms will be our primary outcome; pain severity, pain-related function, opioid use, and quality of life will be the secondary outcomes. The primary end point will be at 12 weeks with a secondary end point at 24 weeks to measure the sustainability of acute effects. Patients will be recruited from a community-based chronic pain clinic in a large urban center in Mississauga, Canada. The meditation program will be delivered in the clinical environment where patients normally receive their chronic pain care by certified meditation teachers who are not regulated health care providers. We will use a mixed-methods design using the multi-level framework to understand the implementation of this particular co-location model.

**Discussion:**

Results of this hybrid evaluation will add important knowledge about the effectiveness of meditation for managing depressive symptoms in people with chronic pain. The implementation evaluation will inform both effectiveness outcomes and future program development, scalability, and sustainability.

**Trial registration:**

ClinicalTrials.gov: NCT04039568. Registered on 31 July 2019.

## Contributions to the literature

This is the first trial examining meditation to improve depression and opioid use in chronic pain.Evidence supporting nonmedication interventions is needed, including how to better integrate them into health care systems. Existing community-based certified teachers can make meditation more accessible and reduce the strain on formal health care services.

## Background

Chronic pain is a common and disabling health condition with significant population-level impacts [1]. The prevalence of chronic pain internationally is approximately 15–20%. In the USA, total health costs and indirect costs such as lost productivity are estimated to be $635 billion per year [2–4]. Comorbid mental illnesses are common in patients with chronic pain, with rates as high as 60% [5] compared to 10–15% in age-matched controls. This comorbidity is associated with poorer overall health outcomes, greater health care utilization, and higher rates of suicide [5]. Living with chronic pain and having a mental illness is also associated with an increased risk of being prescribed an opioid [6], being maintained on long-term opioid therapy (LTOT) [7], and being on higher doses of opioids [8]. Additionally, those with a mental illness who are prescribed opioids have a higher risk of developing a substance use disorder and of overdosing [9], with psychotropic medications prescribed for chronic pain comorbidities compounding the risk of overdose [10–12]. Adding to the complexity of these issues, there is evidence that LTOT is by itself a risk factor for developing de novo depression [13].

Despite the scale and impacts of this comorbidity, there is little evidence-based guidance for the management of mental illnesses in patients with chronic pain. A recent clinical practice guideline for the management of chronic pain [14] has a single recommendation for the management of depression in chronic pain, citing only one controlled trial that investigated a combination of antidepressant therapy and an education program. Clinical experience suggests that pharmacologic approaches to symptom and disorder management can be challenging to implement for people on LTOT due to polypharmacy, a particular challenge for older people [15]. In addition, pharmacotherapy with LTOT carries a risk of overdose and accidental death. Given the complexity and risk associated with pharmacotherapy in patients with chronic pain, there is a need for increased evidence for, and availability of, nonpharmacological treatments to improve quality of life, as well as to decrease pain severity and harms from opioids [16].

A substantial body of evidence suggests that meditation is a promising nonpharmacological intervention for chronic pain. In terms of efficacy, a recent systematic review demonstrated moderate effects for meditation and pain (effect size, 0.33), depression (effect size, 0.30) and anxiety (effect size, 0.38) [17]. Several systematic reviews examining meditation interventions specifically in the chronic pain population have reported small but consistent improvements in pain, function and depression [18–21]. Meditation is commonly sought out by diverse people living with depression and chronic pain and the intervention is well received in these populations [22–24]. *Sahaj Samadhi* Meditation (SSM), a type of automatic self-transcending meditation, is easy to learn and master [25] and its processes can lead to stress reduction and deep relaxation [26]. A randomized controlled trial (RCT) comparing this type of meditation to an active control in adults >55 years of age showed clinically significant reductions (48%) in depressive symptoms [27]. SSM has yet to be evaluated for its effects on depression in people with chronic pain.

Despite evidence of the effectiveness of meditation programs for chronic pain and depression, this intervention has not been widely implemented in North American health systems. The reasons for this are not well understood but may include negative perceptions about the effectiveness of meditation, lack of reimbursement for its delivery and perceived costs, or a mismatch between the holistic and lifestyle approach of meditation and the biomedical orientation that typify contemporary health services. Delivering complementary interventions where patients are usually seen for clinical care by a health professional, such as a physician, nurse, psychologist or physiotherapist, is one approach that has been used to improve the uptake of these interventions. This approach may improve access to these interventions by improving trustworthiness, physical access and familiarity. It may also address human resourcing by providing a means for reimbursement via traditional provider payment models. However, the medicalization of these interventions may have unintended negative consequences at both the intervention and health service level. For instance, it could be argued that health professionals need to focus on their scope of practice and that they do not have time for additional training or to deliver meditation programs. We also speculate that meditation delivered in a clinical environment by a biomedically trained health care provider may change its nature and its effects. There are scores of expert community-based meditation teachers who could provide this intervention without having to divert scarce human health resources.

This approach is in keeping with a stepped-care model of mental health service delivery based on the principle of ‘least burden’, whereby service providers triage patients into the least intensive service that is likely to meet their needs and be effective [28]. The lower tiers include community-based supports that rely on nonspecialists or peers rather than on formal health care resources. However, these lower-tier services are currently underfunded and underutilized in Canada. Investing in them could enhance mental health promotion and reduce the strain on access to higher-tier acute care services [29].

In this context, we posit that there is a need for evidence supporting the use of meditation as a health intervention for those living with chronic pain and comorbid depression. This includes evidence on how to implement such programs in the context of contemporary health systems. These dual and somewhat competing goals can be accomplished with a hybrid design that combines evaluations of both health outcomes of an intervention and the process of its implementation. The scale of the chronic pain and depression comorbidity and its contemporary association with the opioid crisis suggest the need for a more rapid development of usable knowledge which hybrid designs are well positioned to do [30].

This protocol article describes the MEDOTATE study (Meditation for depression and opioid use in chronic pain: an RCT and implementation evaluation), a hybrid type 1 study focusing on the effectiveness of SSM for patient outcomes related to depression, pain, function and quality of life, and which also evaluates the implementation of a collaboration between a community-based chronic pain clinic and certified meditation teachers to provide this intervention. This article describes the study procedures and discusses key methodological decisions and challenges for a hybrid design for a meditation intervention.

We report the protocol for the effectiveness trial using the Standard Protocol Items: Recommendations for Interventional Trials (SPIRIT) statement [31], and describe the intervention using the Template for Intervention Description and Replication (TIDieR) checklist and guide [32]. We report the protocol for the implementation evaluation using the Standards for Reporting Implementation Studies (StaRI) statement [33]. See Fig. 1 for the completed SPIRIT figure presenting the protocol schedule of assessments and interventions. The completed World Health Organization Trial Registration Data Set can be found in Additional file 1.

**Fig. 1 Fig1:**
[figure not shown]
Protocol schedule of assessments and interventions. *Abbreviations:* *BPI* Brief Pain Inventory, *HEP* Health Enhancement Program, *MINI* Mini-International Neuropsychiatric Interview, *SF-36* 36-item Short Form survey, *SSM* Sahaj Samadhi Meditation

## Methods

This study was developed to examine the clinical effectiveness and implementation of an intervention using SSM for older adults living with chronic pain and comorbid depression. The project is being conducted at a community-based chronic pain clinic in a major urban center in Ontario, Canada, with the collaboration of a community-based, non-profit meditation provider. Design of the program included input from a national mental health service delivery and advocacy organization and a person with lived experience, and both will also be integrated in oversight of program delivery and evaluation. The study was approved by the research ethics board of both Mount Sinai Hospital (19-0163-A) and the University of Toronto (00038321); it is funded by the Canadian Institutes for Health Research Opioid Crisis Evaluation Grant (EO1-162072). The trial is registered at clinicaltrials.gov (NCT04039568; https://clinicaltrials.gov/ct2/show/NCT04039568).

SSM is a standardized and manualized meditation program delivered in community settings by certified non-clinician meditation teachers (https://www.artofliving.org/sahaj-samadhi-meditation). Program delivery and teacher certification is conducted by Art of Living (AOL), an international non-profit charitable organization which reaches across 150 countries worldwide. Teachers are required to complete at least 1200 h of personal SSM practice and an intensive teacher training program. SSM is taught in the community through a course called The Art of Meditation, which is a 6-h program over 3 consecutive days without any prerequisites.

Besides its established clinical efficacy for a variety of conditions, meditation carries other advantages as a potential population health intervention. Experience from AOL suggests that the program can be delivered effectively by expert nonclinicians or lay providers (often volunteers); there are many meditation teachers who can be enlisted to provide this intervention, and fidelity of the intervention can be maintained over different sizes of groups. These aspects of SSM suggest the potential for scalability to meet not just clinical needs but also population health needs.

Despite this potential for SSM to beneficially impact the lives of people with chronic pain, mental illness, and using prescribed opioids, there are a variety of real and perceived barriers specifically around reach and access. Some possible, and as yet uninvestigated, barriers include: lack of awareness of the existence of the program by the target audience; lack of awareness of the potential benefits or the nature of the program by the target audience; the monetary cost of the program; physical access to community sites where the program is typically offered; and skepticism of the health benefits by trusted health care providers.

Considering the overall context and the barriers to access, AOL, the Canadian Mental Health Association (CMHA), the Rivlin Medical Group (a community-based chronic pain management clinic), and an academic health services research group are collaborating to develop, deliver and evaluate MEDOTATE. MEDOTATE offers a modified version of SSM by the same teachers as in the community but co-locates its delivery within the context of formal clinical chronic pain care.

As a means of overcoming access barriers, MEDOTATE will offer SSM in the same clinical space and recruitment will occur through the administrative processes that patients are accustomed to using for their routine medical care. SSM will be delivered by three experienced local meditation teachers from AOL, selected by the AOL research director. The AOL research director will also provide ongoing training and troubleshooting for the meditation teachers. Clinic staff and clinicians will also be educated about the program to facilitate service delivery in multiple 1-h in-person informational sessions, email memoranda, and one-on-one discussions.

### Study objectives

There are two broad evaluation objectives. The primary objective is to evaluate the effectiveness of SSM. This evaluation will aim to answer the question: “is SSM effective in improving depressive symptoms and associated variables in chronic pain?”. For this effectiveness objective, we have selected change in depressive symptoms as the primary outcome because of the strength of the pilot data used to inform evaluation design. The secondary effectiveness outcomes will be reduction in pain severity and pain interference, reduction in opioid use, and improvement in quality of life.

The second objective is to evaluate the implementation of SSM in the specific setting of a community-based chronic pain clinic. This part of the evaluation will aim to answer the following questions: “how was SSM implemented in this setting?”, “what were the barriers and facilitators to implementation?” and “how can SSM be translated to other settings?”. This implementation evaluation will help to interpret the effectiveness outcomes and it will be used to inform both implementation and effectiveness outcomes in other, real-world settings such as in multi-provider primary care sites or multi-provider community care sites.

### Study design

MEDOTATE has a hybrid type 1 evaluation design. Hybrid designs aim to blend effectiveness and implementation research to “improve the speed of knowledge creation and increase the usefulness and policy relevance of clinical research”, both of which are imperatives for this proposed evaluation [30]. Specifically, hybrid type 1 designs aim to primarily test the effectiveness of an intervention while gathering information relevant to real-world implementation. In type 1 designs, implementation evaluation is secondary to the primary goal of effectiveness evaluation. This is appropriate given the nature and priorities of the evaluation objectives outlined above where effectiveness of the intervention in this population is not yet established.

Curran et al. [30] note the inherent tensions between effectiveness and implementation evaluations, especially in that they differ in what they test (a clinical intervention versus an implementation strategy), their typical units of randomization and analysis (patient versus organization), and the kinds of outcomes they seek. An important limitation of our approach is that it is not a true evaluation of implementation as there is no a priori commitment on the part of the community-based chronic pain clinic to continue delivering this program beyond the trial period. Despite similar limitations, other groups have successfully executed the implementation component of type 1 hybrid evaluations [34].

Given the character of the hybrid design, a mixed-methods approach to evaluation is appropriate. We will use a QUAN(qual) embedded design, as described by Creswell and Plano Clark [35]. The focus of the evaluation will be on effectiveness in the form of a single-site, single-blinded (investigator and clinician), 12-week RCT powered for the depression outcome and measuring changes in pain, medication use and quality of life as secondary outcomes. Participants will undergo 1:1 randomization to the SSM intervention or to an active control called the Health Enhancement Program (HEP). The two interventions will be run in groups of 10–15 participants on a rolling monthly basis. This will decrease intervention wait times and allow for timely access to the offered interventions and their potential benefits. Additionally, ethics approval for this study was granted under the title “Alternative treatments for depression in chronic pain” to avoid biasing participants with investigators’ hypotheses and to improve retention in the control arm.

Embedded within, and secondary to, this RCT will be an implementation evaluation using both quantitative and qualitative approaches. The implementation evaluation will focus on assessing reach, dose, satisfaction and understanding program implementation facilitators and barriers.

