#### Control intervention

HEP has been designed and used as a manualized active control in other meditation-based intervention trials [37–39]. HEP controls for several nonspecific factors found in a meditation group, including group support and morale, behavioral activation, reduction of stigma, facilitator attention, treatment duration, and time spent on at-home practice (adapted from a published manual [40]). HEP will be tailored to be structurally equivalent to SSM with similar sized groups, meeting schedule, total contact hours, amount of home practice and encouragement to keep practice logs. Participants will learn about health promotion, healthy diet, music and exercise, but will not learn meditation. In HEP, participants get the support of a group and facilitator, and talk through and attempt to implement positive health-enhancing life changes. HEP will be delivered by regulated health care providers not associated with the pain clinic and with formal training by an experienced HEP trainer. There will be no active intervention with respect to prescribed medications during the study for either arm of the study.

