#### Sample size calculation

A practice audit at the pain clinic in which the study will be conducted identified a high degree of comorbid depression and chronic pain in a random selection of 50 patients. Mean PHQ-9 score was 11 (standard deviation 5.7), where scores ≥10 indicate clinical depression. Sixty percent of patients had PHQ-9 scores ≥10 but only 4% had scores ≥20 (severe depression). This audit also identified three pools of patients from which subject participants can be recruited. These include: 1) new consults (30/week of which 38% meet inclusion criteria; *n* = 720 over an estimated 6-month recruitment period); 2) current patients on LTOT prescribed by physicians outside the clinic (*n* = 212); and 3) current patients on LTOT prescribed by clinic physicians (*n* = 194). The estimated total pool of eligible patients to recruit from over a 6-month period is thus about 1100.

In terms of estimated sample size, the primary outcome is continuous as measured by PHQ-9. The standard deviation of the PHQ-9 is 5 units and we anticipate a 2.5-unit difference at the end of the study between the intervention and control groups based on extrapolation of the pilot data [51]. This study is a two-arm RCT; therefore, we used a two-sample *t* test to calculate the sample size to have at least 80% power to detect differences in PHQ-9 scores of 2.5 or larger at 5% type 1 error. The resulting estimated sample size is 64 participants in each arm. We inflated the sample size by 25% to account for dropouts, which is reasonable given an attrition rate of 13% seen in the pilot study [36]. Therefore, we will recruit and randomize a total of 160 participants, with 80 participants in each arm.

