### Data analysis

#### Effectiveness

The primary and secondary outcomes (PHQ-9 score, Brief Pain Inventory, opioid equivalent dose, and 36-item Short From survey) will be measured at baseline and at 12 and 24 weeks. We will examine the distribution of primary and secondary outcomes for normality. If required, appropriate transformation (for example Box–Cox transformation) will be applied to correct the possible non-normality. Our primary and secondary outcomes are continuous and measured over three time points. We will use a longitudinal data analysis approach to asses within-group changes (change over time within each arm) and between-group changes (difference between two groups at each time point) while these assessments are adjusted for potential confounders (such as age, gender, ethnicity and employment status) and the correlation among the repeated measures. We will use a generalized estimation equation method with AR(1) (autoregressive) covariance structure or the random effect method to adjust for the correlation among the repeated measures of the participants. The longitudinal analysis also allows us to compare the change from the baseline at 12 and 24 weeks between intervention and control groups (difference in differences). The analysis will follow the intention-to-treat principle; all participants who are randomized will be included in the analyses and analyzed in the arms to which they were assigned. We will first analyze the data using observed data (complete case), then we impute the missing observations and obtain multiply imputed estimates. There are no prespecified subgroup analyses.

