In terms of providers, the intervention will be provided by expert lay (not health care professional) meditation teachers. This is in contrast to current trends of increasing professionalization of meditation provision as a health care intervention. Our intention in doing so is to acknowledge that there are limitations in human health resources but there are also lay providers who are expert meditation teachers capable of and willing to provide meditation instruction to promote health and well-being. We hope this choice can facilitate scalability.

Finally, we must consider the intervention itself. For the purposes of a clinical trial, meditation programs should be standardized and protocolized to reduce variation between groups which can mediate effects. However, as with other behavioral interventions, it is important to acknowledge the socialized nature of the meditation instruction and practice. While it is relatively easy to reduce variation in RCTs assessing medications, it is more challenging to reduce variations in human interactions which depend more on time, space and context. For example, the life experiences of participants will be acknowledged and attended to during the meditation intervention. Different cohorts will have different sets of experiences that will determine the specific dynamics of how the intervention is delivered. Variation between groups cannot be completely eliminated. However, standardization and protocolization of intervention delivery can minimize this variation. These effects can be further minimized by randomization and an active control that is also a behavioral, group-based intervention.

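### Both arms are treated in groups of 10–15, but neither the sample size nor the analysis model allows for correlation within a treatment group

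*Protocol article*

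**What the plan says.** **Unit of randomisation and delivery.** Under Study design, "Participants will undergo 1:1 randomization to the SSM intervention or to an active control", so individuals are allocated. The same section then says "The two interventions will be run in groups of 10–15 participants on a rolling monthly basis". The control arm is grouped too: under Control intervention, "HEP will be tailored to be structurally equivalent to SSM with similar sized groups, meeting schedule".

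**Sample size.** The calculation rests on a two-sample t test, and its stated aim is "to have at least 80% power to detect differences in PHQ-9 scores of 2.5 or larger at 5% type 1 error". The standard deviation is taken as 5. The section then reports its result: "The resulting estimated sample size is 64 participants in each arm". The only inflation is 25% for dropout, giving 80 per arm and 160 in total.

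**Model.** The Effectiveness part of Data analysis names a generalised estimating equation with AR(1) structure, or "the random effect method to adjust for the correlation among the repeated measures of the participants". Its example covariates are age, gender, ethnicity and employment status. It names no term for group, cohort or facilitator.

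**Discussion.** The article accepts that cohorts will differ in how the intervention plays out and that "Variation between groups cannot be completely eliminated". It relies on standardised delivery, randomisation and a group-based active control to keep this small.

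**The concern.** People in one treatment group share sessions, a teacher or facilitator, and each other for 12 weeks, so their outcomes may be correlated. Randomisation cannot remove this, because the correlation arises after allocation. A grouped control arm does not cancel it either; it adds a second set of clusters.

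The two harms are alternatives:

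- **Groups left out of the model:** the standard error of the 12-week PHQ-9 difference is too small, and the primary test rejects a true null hypothesis more often than 5% of the time.
- **Groups put into the model:** the test is valid, but 160 participants no longer give the stated 80% power.

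The choice matters because the Discussion presents the trial as powered for depression as its primary outcome, and the Dissemination plan foresees using the result to advocate wider access.

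**Working it through.** **Inputs from the protocol article.** Difference 2.5, SD 5, 5% type I error (taken as two-sided, which reproduces the stated figure), 64 analysed and 80 randomised per arm, groups of 10–15, pilot attrition 13%.

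**Assumption.** The protocol gives no ICC. A range of 0.01 to 0.10 is used, the same in both arms.

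**Step 1: the plan's own figure.** The noncentrality is 2.5 / (5 × √(2/64)) = 2.83. With 126 degrees of freedom the noncentral t gives 80.1% power (79.5% at 63 per arm). So 64 per arm is right for independent participants. Then 64 × 1.25 = 80, which covers a 20% loss.

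**Step 2: groups.** Groups per arm, k = 80/15 to 80/10 = 5.3 to 8, or about 11–16 in total. After a 20% loss the analysed group size is m = 8 to 12.

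**Step 3: design effect.** DE = 1 + (m − 1) × ICC. At ICC 0.05 this is 1 + 7 × 0.05 = 1.35 to 1 + 11 × 0.05 = 1.55.

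**Step 4: type I error if groups are ignored.** 2 × (1 − Φ(1.979/√DE)), where 1.979 is the t critical value on 126 degrees of freedom.

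**Step 5: power if groups are allowed for.** The noncentrality becomes 2.83/√DE. Power is read from the noncentral t, first with 126 degrees of freedom and then with the group-level 2(k − 1), which is 8.7 to 14.

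| Assumed ICC | DE (m = 8, 12) | Type I error, formula | Type I error, simulated ANCOVA, 6 or 8 groups per arm | Power, participant df | Power, group df |
|---|---|---|---|---|---|
| 0.01 | 1.07, 1.11 | 5.6–6.0% | not run | 76–77% | 66–72% |
| 0.02 | 1.14, 1.22 | 6.4–7.3% | 6.8–8.3% | 72–75% | 62–69% |
| 0.05 | 1.35, 1.55 | 8.9–11.2% | 10.3–11.8% | 62–68% | 52–62% |
| 0.10 | 1.70, 2.10 | 12.9–17.2% | 14.5–17.3% | 49–58% | 41–52% |

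The two type I error columns together give about 6%, 6–8%, 9–12% and 13–17%. A separate simulation of a t test that ignores groups (40,000 runs per setting) gave 5.6%, 6.6%, 9.3% and 13.3% with 8 groups of 8 per arm. With 6 groups of 11 it gave 5.7%, 7.5%, 10.9% and 17.1%. A layout just outside the range, 5 groups of 13, gave 6.4%, 7.9%, 12.4% and 19.0%.

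The group-df column is the cautious end. At ICC 0 the same formula gives 75% (groups of 10) and 71% (groups of 15), so part of that loss is the price of having few groups.

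**Step 6: detectable difference at ICC 0.05.** 2.5 × √1.35 = 2.9 to 2.5 × √1.55 = 3.1 points on participant-level degrees of freedom.

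**Step 7: lower attrition.** With the pilot's 13%, 80 × 0.87 = 69.6, about 70 per arm. Then m = 10 × 70/80 to 15 × 70/80 = 8.75 to 13.1, and power under independence is 83.6%. On participant-level degrees of freedom, power is 79–81% at ICC 0.01, 75–78% at 0.02 and 64–70% at 0.05. On group-level degrees of freedom it is 70–76% at ICC 0.01.

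**The case against.** **The analysis plan is not shown.** It could add a group term, and the article does not say that groups will be ignored. This stands in part. A reader might infer that the trial's p-values will certainly be too small, but the document supports this only if the analysis follows the model as described. The article does, however, name the correlation it adjusts for, and it is the wrong one to stop at. A later analysis plan also cannot restore power already fixed by 160 participants.

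**The plan has slack.** A reader might infer that 80% power needs an ICC of exactly zero. That is too strong. It applies to 64 analysed per arm in an unadjusted comparison, and with the pilot's attrition an ICC of 0.01 is roughly absorbed on participant-level degrees of freedom. Baseline adjustment might help further. Assume a baseline correlation of 0.5 (not in the protocol) that removes a quarter of the variance and none of the treatment-induced group variance, so that DE becomes 0.75 + (m − 1) × ICC. Power with 64 analysed at ICC 0.01 is then 86–87% (77–83% on group-level degrees of freedom). The sample size section claims no such gain, and a plain change score gains nothing at that correlation because its variance is 2 × (1 − 0.5) = 1 times the original. At ICC 0.05 power stays below 80% even with this adjustment and 70 analysed. None of this repairs the type I error of a model without groups.

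**The Discussion describes delivery, not correlated outcomes.** This is fair. It says that cohorts shape how the intervention is delivered and that variation can affect results; it does not speak of correlated outcomes or a shared facilitator. The measures it lists may reduce the variation, but they do not account for what remains.

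**The size rests on an assumed ICC.** This stands in full. Nothing in the protocol favours 0.05 over 0.01.

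**Conclusion.** The point holds. The sample size and the described model both treat participants as independent across a design in which both arms are delivered in about 5–8 groups each, and the protocol itself expects variation between groups. For any positive ICC, either the type I error exceeds 5% (groups ignored) or power at 64 analysed per arm is below the stated 80% (groups modelled). It would be wrong to read these as happening together: the power figures describe an analysis that accounts for groups, and the type I error figures describe one that does not.

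The direction does not depend on the assumed ICC; the size does. The effect is small at 0.01, where pilot-level attrition nearly offsets the power loss on participant-level degrees of freedom, and serious at 0.05 and above. Because it bears on the validity of the primary test and can be corrected in wording, it should be corrected before the data are analysed.

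**What to change.** **Data analysis, Effectiveness.** Add a random intercept for treatment group within arm to the longitudinal model, with Kenward–Roger or Satterthwaite degrees of freedom. If GEE is kept, do not use an uncorrected sandwich estimator clustered on group with about 11–16 groups. Arm-specific group variances belong in a sensitivity analysis only, because 5–8 groups per arm estimate them poorly.

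**Data collection.** Record each participant's treatment group explicitly. The article describes attendance and practice logs but does not say that they carry a group identifier.

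**Sample size calculation.** Keep 160 participants and restate the power, or the detectable difference, over a stated ICC range.

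**Cost.** A less favourable stated power, a slightly more complex model and one extra data field. No additional participants and no change to delivery are needed.
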